**Other jobs**					
Distribute experimental drugs	□	□	□		
Recall test drug		□	□	□	
Record AEs and combined medications		□	□	□	□
Compliance judgment		□	□	□	□

### Outcome measures

#### Primary outcome

Composite Endpoint (35)
Death due to cardiovascular and cerebrovascular reasons:
1.1.Death due to cardiac arrest (with symptomatic myocardial ischemia, new ST-segment elevation or left bundle branch block, and angiographic or autopsy evidence of new thrombosis).1.2.Death due to cardiovascular causes: caused by acute myocardial Infarction (MI), heart failure, stroke, other cardiovascular causes, or without clear non-vascular cause.1.3.Sudden cardiac death: unexpected death due to cardiac causes in a previously stable condition.1.4.Death occurring within up to 30 days after a documented acute MI, without conclusive evidence of another cause; or death occurring based on clinical presentation and ECG evidence before biomarker confirmation of myocardial necrosis.1.5.Death occurring within up to 30 days after an intracranial hemorrhagic or non-hemorrhagic stroke, based on clinical presentation, neuroimaging, or autopsy, without conclusive evidence of another cause of death.1.6.Other cardiovascular or cerebrovascular causes of death.Non-fatal myocardial infarction (MI):
2.1.Spontaneous MI.2.2.ST-segment elevation MI (STEMI).2.3.Non-ST-segment elevation MI (NSTEMI).2.4.Percutaneous coronary intervention (PCI)-related MI.2.5.Coronary artery bypass grafting (CABG)-related MI.2.6.Silent acute MI.Non-fatal stroke:
3.1.Acute neurological dysfunction attributed to a vascular cause, documented by CT or MRI, with other causes excluded.3.2.Transient ischemic attack with symptoms lasting <24 h but with corresponding new imaging evidence (optional predefined criterion, might be moved to secondary depending on standard definitions).3.3.Micro-bleeds: small, round, hypointense lesions <5-10 mm on MRI (often considered a biomarker rather than a clinical event; might be more suitable for exploratory/system bio indicators).

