**Methods:**

This is a randomized, double-blind, placebo-controlled, multicenter trial. A total of 530 participants aged ≥65 years, diagnosed with MetS and the TCM pattern of Qi Deficiency and Blood Stasis, and at high CCV risk, will be enrolled. They will be randomly assigned (1:1) to receive either TJC or a matched placebo, in addition to standard care, for 26 weeks, followed by a 26-week follow-up. The primary endpoint is the composite of 3P-MACE (cardiovascular death, non-fatal myocardial infarction, non-fatal stroke). Secondary endpoints include metabolic parameters, vascular assessments, TCM symptom scores, and quality of life. Omics analyses will explore potential mechanisms. The trial was registered on ClinicalTrials.gov (NCT06908473).

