**Data collection**					
Written informed consent	□				
Inclusion/exclusion criteria	□				
Demographics	□				
Obtain central random number	□				
Previous history, medical history, and allergies	□				
Comorbidities and co-medications	□	□	□	□	□
Safety evaluation					
Vital signs and physical examination	□	□	□	□	□
Blood routine, Urine routine, Fecal routine	□		□	□	
Liver function(ALT, AST, ALB), kidney function(UN, Cr, UA, eGFR)	□		□	□	
12-Lead ECG	□		□	□	□
Efficiency evaluation					
Composite outcome measures	□	□	□	□	□
Preset exploration indicators	□	□	□	□	□
BMI, waist to hip ratio, body fat analysis	□	□	□	□	□
Blood glucose, blood lipids, blood pressure	□		□	□	□
Fasting insulin, C-peptide, HOMA-IR	□		□	□	□
Cardiovascular and cerebrovascular risk index	□		□	□	□
Troponin, cardiac enzymes, BNP	□		□	□	□
Vitamin D	□			□	□
UACR	□		□	□	□
Cardiac color doppler ultrasound	□			□	□
Neck vascular ultrasound	□			□	□
Traditional chinese medicine syndrome points	□	□	□	□	□
Quality of life rating	□	□	□	□	□
Omics analysis	□			□	

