## Discussion

Driven by the high prevalence of MetS, its associated elevated cardiovascular and cerebrovascular risk, and the current lack of clarity regarding the effect of Tongmai Jiangtang Capsule—a glucose- and lipid-lowering agent—on cardiovascular events in MetS patients, there is an urgent need to fill the gap in high-level evidence for TCM compounds in this domain, prompting the initiation of this study. The adoption of a multi-center, double-blind RCT design represents the current “gold standard” for validating intervention efficacy. The multi-center design, by enrolling patients from diverse geographical regions (North, East, South, Southwest, Northwest China) and lifestyles (urban/rural), significantly enhances sample representativeness and reduces the “selection bias” inherent in single-center studies. Compared to other TCM studies, the multi-center nature of this trial better aligns with the characteristics of MetS, which involves “multi-system involvement and high population heterogeneity,” thereby strengthening the generalizability of the findings.

Notably, this study sets the primary endpoint as 3P-MACE (including non-fatal myocardial infarction, non-fatal stroke, and cardiovascular death). This “hard endpoint” directly reflects clinical outcomes and holds greater clinical significance compared to surrogate markers commonly used in traditional studies (39) [e.g., carotid intima-media thickness [IMT], flow-mediated dilation [FMD]]. The secondary endpoints encompass metabolic parameters and vascular-related indicators, addressing the developmental cascade of MetS: “metabolism-vascular injury-cardiovascular events.” This “stratified endpoint design” breaks through the limitation of traditional TCM research that often “emphasizes symptoms over hard outcomes,” better aligning with the core requirement of modern evidence-based medicine for demonstrating “clinical value.”

TJC has been marketed for years. Previous clinical trials and observational studies indicate that its adverse reactions are primarily mild gastrointestinal discomfort, with no reports of severe hepatic or renal impairment, ensuring good patient tolerability. Multiple clinical studies suggest that TJC can improve insulin resistance, effectively alleviate diabetic neuropathy and nephropathy, and improve prognosis in diabetic patients with cerebral infarction (32, 40).

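### The stroke component of the primary composite is left undecided on TIA with new imaging (item 3.2) and MRI micro-bleeds (item 3.3), and item 3.3 does not fit the hard 3P-MACE that the protocol claims

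*Protocol article*

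**What the plan says.** The Abstract (Methods) states: "The primary endpoint is the composite of 3P-MACE (cardiovascular death, non-fatal myocardial infarction, non-fatal stroke". The Discussion calls this a hard endpoint and says that it "directly reflects clinical outcomes and holds greater clinical significance compared to surrogate markers commonly used in traditional studies".

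The operative definition is under Outcome measures, Primary outcome. It lists three items as non-fatal stroke:

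- **3.1** "Acute neurological dysfunction attributed to a vascular cause, documented by CT or MRI, with other causes excluded".
- **3.2** "Transient ischemic attack with symptoms lasting <24 h but with corresponding new imaging evidence", followed by the note "optional predefined criterion, might be moved to secondary depending on standard definitions".
- **3.3** "Micro-bleeds: small, round, hypointense lesions <5-10 mm on MRI (often considered a biomarker rather than a clinical event". The same note goes on to suggest that the item may sit better with the exploratory or systems-biology measures.

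The exploratory and secondary outcome lists contain neither 3.2 nor 3.3. The Safety assessment section has a blinded CEC adjudicate suspected endpoints against criteria set in advance, without saying which stroke items those criteria include. Table 1 has two ultrasound rows, one cardiac and one "Neck vascular ultrasound", and no row for brain MRI. The Sample size calculation is based on the composite primary outcome.

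**The concern.** A confirmatory trial needs one primary outcome, settled before events are counted. Here the definition carries what read as open drafting remarks: one item is described as both predefined and optional, and another is doubted in the same line that lists it. Two adjudicators could follow this text faithfully and count different patients.

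Item 3.3 raises a further problem. The case for the trial is that it measures clinical events and not surrogates. An MRI lesion that the protocol itself says is often regarded as a biomarker is not such an event. If it were counted, part of the primary result would reflect who happened to be scanned and what lesions they already had.

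**Working it through.** This is a check of the text. Arithmetic enters only in steps 1, 4 and 5.

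**1. Is the status of each item settled anywhere?**

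| Place in the article | Item 3.2 | Item 3.3 |
|---|---|---|
| Primary outcome | listed, but optional and movable | listed, but possibly better as exploratory |
| Pre-specified exploratory outcomes | absent | absent |
| Secondary outcomes | absent | absent |
| Safety assessment (CEC) | not named | not named |

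Two items, each in or out, give 2 × 2 = 4 composites that the text allows.

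**2. Does each item fit a hard clinical endpoint?**

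| Item | Symptoms or dysfunction required | New or acute required | Status |
|---|---|---|---|
| 3.1 | yes | yes (acute) | fixed |
| 3.2 | yes | yes (new imaging evidence) | open |
| 3.3 | no | no | open |

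Only 3.3 conflicts with the Abstract and the Discussion. Item 3.2 is undecided, but it is a clinical event. Item 3.1 gives no minimum symptom duration, so an event described in 3.2 could arguably qualify under 3.1 as well. Leaving 3.2 out would therefore need a matching clarification in 3.1.

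**3. Could 3.3 be applied consistently if kept?**

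- The size limit spans 5 to 10 mm. A 7 mm lesion counts under the upper limit and not under the lower one.
- None of the five visits in Table 1 has brain MRI, including baseline. Detection would rest on scans done for other reasons, with no trial baseline to separate old lesions from new.
- Inclusion criterion 4.2 admits patients with earlier stroke or TIA, so lesions that predate randomization are a real possibility.

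**4. When must the question be closed?** The Statistical analysis section has the SAP finalized before database lock and unblinding. Recruitment was to start in May 2025 and take up to 3 years, and each patient is followed to week 52. The last visit may thus fall about 3 + 1 = 4 years after the first enrolment. The stated deadline allows the choice after most events have occurred.

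**5. Does the sample size pin down the composite?** The stated inputs are a difference of 0.15, one-sided α = 0.025, power 0.90, 1:1 allocation and 20% dropout. The stated result is 265 per group. The pooled formula is

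n = [1.960·√(2p̄(1−p̄)) + 1.282·√(p₁(1−p₁) + p₂(1−p₂))]² / 0.15².

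No arm-specific rates are given, so they have to be assumed:

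| Assumed rates | n evaluable per group | n / 0.8 |
|---|---|---|
| 43% vs 28% | 212 | 265 |
| 30% vs 15% | 161 | 202 |
| 20% vs 5% | 101 | 127 |

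The pair 72% vs 57% also gives 265. So 265 is reachable and is not shown to be wrong. But the calculation does not say which events make up the composite, and the rate behind it has no clear meaning until the components are fixed.

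**The case against.** The strongest reply is that safeguards exist. The CEC is blinded and works to criteria set in advance, investigators stay blinded until the database is locked, and the SAP is to be final before unblinding. The note on 3.2 ties any move to standard definitions and not to results. The full protocol or CEC charter may already hold a clean definition. Event-driven brain imaging also need not appear in a visit schedule, and item 3.1 already presupposes CT or MRI at the event.

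Most of this is fair. It limits the risk of a results-driven change, and it means that the missing MRI row matters only if 3.3 stays. It does not cure the defect. The article does not merely omit a detail: it states a primary outcome with open options. The safeguards do not say what counts, they allow the choice after events have accrued, and they cannot supply a baseline scan.

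Four stronger readings are tempting, and the documents do not support them:

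- **The CEC must count incidental or old lesions as strokes.** The same line that lists micro-bleeds doubts their place, so the text supports only that the matter is unsettled.
- **The sponsor could choose components by result.** Blinding and the timing of the SAP work against this.
- **A given share of events, or a given dilution of the effect, would come from micro-bleeds.** That needs the micro-bleed rate, the clinical event rate, the overlap between them (each patient counts once in a proportion) and the effect of treatment on micro-bleeds. The article gives none of these.
- **The Hirudo component would push the composite against the drug.** The safety section names intracranial hemorrhage and other serious bleeding, not micro-bleeds, so no direction can be stated.

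**Conclusion.** The point holds and needs correction before events are adjudicated. As written, the stroke component of the primary outcome is not fixed, and four versions are compatible with the text. Item 3.3 contradicts the claim of a hard 3P-MACE endpoint and cannot be applied consistently with the scheduled assessments. Item 3.2 is at fault only for being undecided.

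This conclusion rests on the wording of the article alone and on no assumed rate. Its numerical effect on event counts, risk difference or power cannot be given. If the full protocol or CEC charter already contains a settled definition, the remaining task is to bring the published text into line with it.

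**What to change.** - Move item 3.3 out of the primary composite and report micro-bleeds as exploratory, in patients who happen to have MRI.
- Decide item 3.2 now. Either choice is defensible, since it is a symptomatic event with new imaging. If it is out, list it as a secondary or exploratory outcome and clarify item 3.1 so that the same event does not re-enter there.
- Delete the conditional notes from both items.
- Put the identical definition into the CEC criteria before any event is adjudicated. If adjudication has begun, apply the definition to all events while still blinded, and record the date of the change.
- Align the Abstract, Primary outcome, Safety assessment, Sample size calculation and Discussion. In the sample size section, state which components the 15% difference refers to.

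The cost is an amendment of wording and of the CEC criteria, with no new visits or tests. The downside is that some events may no longer count towards the primary outcome. How many cannot be estimated from the article.

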### Pre-specified exploratory outcomes

Composite cardiovascular outcome (cardiovascular death, non-fatal MI, non-fatal stroke, coronary revascularization, or hospitalization for unstable angina or heart failure).All-cause mortality.Renal and glucose-related retinal microvascular composite outcomes.
3.1.Renal composite outcome: New-onset persistent macroalbuminuria (UACR >300 mg/g), or persistent doubling of serum creatinine from upper limit of normal or eGFR <45 mL/min/1.73m^2^, or requiring continuous renal replacement therapy or death due to renal disease.3.2.Diabetic retinopathy microvascular composite outcome: Requiring retinal photocoagulation or intravitreal injections, vitreous hemorrhage, or blindness.

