### Inclusion criteria

Age ≥65 years.Meets the diagnostic criteria for MetS.Meets the pattern diagnosis criteria for Qi deficiency and blood stasis.High cardiovascular and cerebrovascular risk population, meeting any one of the following criteria (35):
4.1.History of myocardial infarction.4.2.History of stroke or transient ischemic attack.4.3.History of coronary, carotid, or peripheral arterial revascularization.4.4.Coronary, carotid, or lower extremity arterial stenosis >50%.4.5.Positive exercise stress test or documented symptomatic coronary artery disease by any cardiac imaging, or unstable angina with ECG changes.4.6.Chronic heart failure (NYHA class II-III).4.7.Chronic kidney disease (eGFR <60 mL/min/1.73m^2^).

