### Safety assessment

1.Safety evaluation indicators

Safety evaluation indicators include physical examination, vital signs (heart rate, respiration, temperature, blood pressure), laboratory tests, and adverse events (AEs), including severe adverse events (SAEs). Laboratory tests include complete blood count, urinalysis, blood biochemistry, and 12-lead ECG. Blood biochemistry will specifically include alanine aminotransferase (ALT), aspartate aminotransferase (AST), albumin (ALB), creatinine (Cr), blood urea nitrogen (BUN), and estimated glomerular filtration rate (eGFR).

During the treatment period, investigators must carefully observe and record all AEs and unexpected toxic side effects (including symptoms, signs, and laboratory abnormalities). Regardless of whether an AE is considered related to the investigational product, it must be documented in detail in the case report form (CRF), including time of onset, symptoms, signs, severity, duration, laboratory values, treatment administered and outcome, time elapsed, and follow-up time.
2.Clinical Events Committee and Independent Data Monitoring CommitteeA Clinical Events Committee (CEC) comprising a cardiologist, a neurologist, and an imaging specialist has been established. The CEC will adjudicate all suspected cardiovascular and cerebrovascular endpoints (including 3P-MACE) and all serious adverse events (SAEs) in a blinded manner using pre-defined diagnostic criteria.

An Independent Data Monitoring Committee (IDMC) composed of a cardiovascular specialist, a neurologist, and a biostatistician has also been established. The IDMC is independent of the sponsor and investigators.
3.Pre-specified SAEs related to TJC componentsIn consideration of the Hirudo (Shuizhi) component, the following events are pre-specified as SAEs requiring immediate reporting and adjudication:① bleeding requiring platelet transfusion or hospitalization; intracranial hemorrhage; gastrointestinal bleeding requiring transfusion; clinically significant mucosal bleeding requiring medical intervention; ② prolongation of APTT or PT > 1.5× upper limit of normal (ULN); platelet count < 50 × 10⁹/L; ③ ALT or AST elevation > 3× ULN; eGFR reduction > 30% from baseline or < 45 mL/min/1.73 m^2^; serum creatinine doubling from baseline.

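### The exploratory renal composite measures creatinine doubling from the upper limit of normal, so that criterion adds no event beyond eGFR <45 and some doublings from the patient's own baseline go uncounted

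*Protocol article*

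**What the plan says.** Under Pre-specified exploratory outcomes, item 3.1, the renal composite is met by any one of several events. The first is "New-onset persistent macroalbuminuria (UACR >300 mg/g" in the protocol's unit. The next two are "persistent doubling of serum creatinine from upper limit of normal or eGFR <45 mL/min/1.73m^2". Continuous renal replacement therapy and renal death complete the list.

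Under Safety assessment, item 3, the pre-specified SAEs include "eGFR reduction > 30% from baseline or < 45 mL/min/1.73 m^2" and, separately, "serum creatinine doubling from baseline". The article therefore holds two reference points for a doubling of creatinine: a laboratory limit for the outcome and the patient's own starting value for the SAE.

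Two other places matter. Participants are aged 65 or over, and one of the seven routes to high-risk status is "Chronic kidney disease (eGFR <60 mL/min/1.73m^2"; the other six do not require reduced kidney function. Table 1 schedules "kidney function(UN, Cr, UA, eGFR" at screening/baseline, Week 12 and Week 26, so a baseline creatinine exists for every participant.

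**The concern.** A doubling is a statement about change. If it is tied to the ULN, the criterion becomes a fixed threshold of creatinine at or above 2 × ULN. A patient who starts below the ULN must then rise by 2 × ULN / baseline, which always exceeds two-fold.

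Two consequences follow if this is applied as written. First, a fixed creatinine threshold that high may lie wholly inside the region already covered by eGFR <45, in which case the criterion does no work. Second, a patient with well-preserved function can lose a large share of it, double the creatinine, and count under neither criterion.

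At stake is whether the composite can register a loss of kidney function that starts from a good baseline. The primary endpoint, the secondary outcomes and the sample size are not touched.

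**Working it through.** The article states no event count or power for the renal composite, so there is no figure to reproduce. The check has two parts: whether 2 × ULN always implies eGFR <45, and which doublings from baseline leave eGFR at 45 or above.

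**Inputs from the article:** age ≥65; the or between the criteria; the eGFR cut-off of 45; baseline creatinine collected at Visit 1.

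**Assumptions (not in the article):** ULN 97–133 µmol/L in men and 73–106 µmol/L in women; eGFR by CKD-EPI 2009, CKD-EPI 2021, MDRD or the Chinese-modified MDRD. eGFR is in mL/min/1.73 m² throughout.

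**Step 1. eGFR at creatinine = 2 × ULN (range over the four equations)**

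| Sex, ULN (µmol/L) | 2 × ULN | eGFR, age 65 | eGFR, age 80 |
|---|---|---|---|
| Man, 97 | 194 | 30.3–32.5 | 27.4–30.3 |
| Man, 104 | 208 | 27.9–29.9 | 25.2–27.8 |
| Man, 133 | 266 | 20.8–22.3 | 18.7–20.5 |
| Woman, 73 | 146 | 31.2–35.3 | 29.0–34.0 |
| Woman, 81 | 162 | 27.7–31.0 | 25.6–29.9 |
| Woman, 106 | 212 | 20.3–22.3 | 18.5–21.4 |

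Every value is below 45. Higher creatinine or greater age lowers it further. So each creatinine event is already an eGFR event. This holds whether the word persistent governs the creatinine criterion alone or both, because a persistent creatinine at 2 × ULN implies a persistent eGFR below 45.

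**Step 2. How low the ULN would have to be for the criterion to add anything**

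At age 65, eGFR equals 45 at a creatinine of 138–148 µmol/L in men and 106–120 in women. Half of each gives the ULN needed: 69–74 in men and 53–60 in women. Every ULN tried is higher than this.

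**Step 3. Which doublings escape both criteria**

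Over ages 65–85, eGFR reaches 45 at a creatinine of about 125–148 µmol/L in men and 99–120 in women. A doubling that ends below that point leaves eGFR above 45. The baseline must therefore be below about 62–74 in men or 49–60 in women, which corresponds to a baseline eGFR above about 85–106, depending on age and equation.

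**Step 4. Examples (CKD-EPI 2009 and 2021)**

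- Man aged 66, ULN 104: creatinine 60 to 120, eGFR 100–103 to 54–58. The fall is 1 − 54/100 = 46% or 1 − 58/103 = 44%. The creatinine criterion would require 2 × 104 = 208, and 208/60 = 3.5-fold. **Missed by both criteria.**
- Woman aged 67, ULN 81: creatinine 48 to 96, eGFR about 97–101 to 53–56. The creatinine criterion would require 2 × 81 = 162, and 162/48 = 3.4-fold. **Missed by both criteria.**
- Man aged 70: creatinine 80 to 160, eGFR 86–91 to 37–40. Below 2 × 104 = 208, so missed by the creatinine criterion, but **caught by eGFR <45**.

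The first two patients meet the SAE rule for doubling from baseline and also its rule for an eGFR fall of more than 30%, yet are not renal events through the creatinine or eGFR criteria of item 3.1.

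**The case against.** The strongest reply is that the outcome is a composite, and the composite misses far less than its creatinine criterion does. That stands. Doublings from a baseline eGFR below about 85 are counted through eGFR <45. The trial recruits older, high-risk people, with heart failure and chronic kidney disease among the entry routes, so those starting above 85–106 are probably a minority. A missed event also needs the doubling to persist, and creatinine is scheduled only twice after baseline. The number among 530 participants could be very small.

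A reader might infer that most true doublings are lost from the outcome. The article does not support that. Any such share depends on an assumed creatinine distribution, and on treating a doubling as equally likely at every level of baseline function.

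A reader might also infer that the composite loses its most specific events. It does not: for someone starting below the ULN, 2 × ULN is the stricter threshold, so moving to baseline gains sensitivity rather than specificity.

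Finally, it is tempting to treat the difference between the outcome and the SAE list as an error in itself, or to impose one definition on both. The two lists serve different purposes. The SAE list calls for immediate reporting, has no persistence requirement and includes an eGFR fall of more than 30%. Some disagreement between the tables would remain after any edit to item 3.1. What survives all this is narrower: the outcome's creatinine criterion, as stated, does no work.

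**Conclusion.** The point holds as a minor one. For every ULN and equation tried, creatinine at or above 2 × ULN at age 65 or over means an eGFR of about 19–35, so the creatinine criterion adds no event to eGFR <45. Persistent doublings from a baseline eGFR above about 85–106 are counted by neither criterion. The redundancy is robust over the assumed ranges. The number of missed doublings in this trial cannot be derived from the article and is probably modest.

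This is a stated rule that does not function, not a detail left to the SAP: the article names the reference value, and a SAP that followed it would carry the fault forward.

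It is separate from another weakness in the same sentence. The eGFR <45 criterion has no stated new-onset condition, although eGFR <60 is an entry route, so it could count patients already below 45 at entry. Correcting the creatinine reference does not cure that.

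**What to change.** In item 3.1, change the reference for the creatinine doubling from the ULN to the patient's baseline (Visit 1) value, and keep the word persistent. Make the change in the protocol or SAP before unblinding, so that the choice of reference cannot be seen as data-driven. Leave the SAE reporting rule under Safety assessment unchanged, including its lack of a persistence requirement.

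The cost is one line of wording. No new data are needed, since creatinine is already measured at Visit 1, Week 12 and Week 26. The downside is that a few patients with a low baseline creatinine will qualify at values only moderately above normal, such as 120 µmol/L against an assumed ULN of 104 in the first example. Keeping the persistence requirement limits how many of these are noise.
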